#### **1.2 Secondary**

- 1) To examine the role of anastrozole in preventing oestrogen receptor positive breast cancer.
- 2) To examine the effect of anastrozole on other cancers, cardiovascular disease, fracture rates, and non-breast cancer deaths.
- 3) To examine tolerability and acceptability of side effects experienced by women on the study. (Met at LPLT – March 2017).

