#### **4.5.1.2 Post-treatment Follow-up Questionnaires (PTQ) - Years 6 – 10**

After 5 years of active treatment, women will continue to be followed up for clinical events of interest including SAEs, via the 'post-treatment follow-up' CRF for a further 5 years.

These will specifically ask the patients about the following events: -

- Breast cancer and DCIS (endpoint not requiring reporting)
- Stroke or TIA
- Other cancers (except basal cell carcinoma, squamous cell carcinoma of the skin and carcinoma in situ of the cervix)
- Cardiovascular events e.g. angina, heart attack, hypertension
- Thromboembolic events e.g. deep vein thrombosis, pulmonary embolism, phlebitis
- Osteoporosis/Broken/fractured bone
- Deaths

The decision to collect events of interest rather than asking about all AEs is based upon the following

- 5x half-life of IMPs will be reached within 35 days i.e. a short time period and therefore long term monitoring is not required.
- Except for certain conditions (endometrial cancer, osteoporosis/fracture, cardiovascular disease), further side-effect either stop with IMP washout or are of negligible significance.
- The safety profiles of Anastrozole has already been well-established across multiple trials and long follow up periods (as of 31 July 2016, the total cumulative exposure figure for ARIMIDEX in the marketed setting is calculated to be in excess of 8 million patient years)
- This is an ageing trial population with many AEs meeting the definition of SAEs but that are not of direct relevance to the trial objectives. To date, approximately 6% of reported SAEs in the post-treatment phase have been defined as causally related by the site investigator. Efforts should be re-focused on the collection of events known to be IMP related and the identification of any emerging safety signals. A more defined scope of AE collection is therefore warranted.

- All identified SARs/SUSARS will meet expedited reporting timeframes.

Sites have the option to conduct this by clinic, phone, postal questionnaire or if the patient is not able to be contacted, consultation of hospital records. This will collect data required to meet the primary, secondary and exploratory objectives of the trial.

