**Table 1. Events of Interest/ICD code**

| Event                       | ICD-code                                                                                 |
|-----------------------------|------------------------------------------------------------------------------------------|
| Breast cancer               |                                                                                          |
| Breast cancer (invasive)    | C50.0-9                                                                                  |
| Breast cancer (DCIS)        | D05.0/1/7/9                                                                              |
| Other malignant cancer      | C00-43, C45-49 and C51-97 (all sub-codes)
This includes all other cancers except skin |
| Other events                |                                                                                          |
| Pulmonary embolism          | I26.0, I26.9                                                                             |
| Deep vein thrombosis        | I80.2                                                                                    |
| Cerebrovascular events      | I63 (all sub-codes), I64                                                                 |
| Cardiac arrest              | I46 (all sub-codes)                                                                      |
| Acute myocardial infarction | I21 (all sub-codes), I22 (all sub-codes)
I22 is for subsequent myocardial infarctions |
| Heart failure               | I50 (all sub-codes)                                                                      |

|                                     |                                                                                                                                                                                                                                                             |
|-------------------------------------|-------------------------------------------------------------------------------------------------------------------------------------------------------------------------------------------------------------------------------------------------------------|

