| Transient cerebral ischaemic attack | G45.8, G45.9                                                                                                                                                                                                                                                |
| Hypertension                        | I20, I15 (all sub-codes), I27 (all sub-codes)                                                                                                                                                                                                               |
| Fractures                           | M80 (all sub-codes), T02.9, T08, T10, T12, S02 (all sub-codes), S12 (all sub-codes), S22 (all sub-codes), S32 (all sub-codes), S42 (all sub-codes), S52 (all sub-codes), S62 (all sub-codes), S72 (all sub-codes), S82 (all sub-codes), S92 (all sub-codes) |

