### **Patient identifiable data and raw extracts**

PID including the participants full name, NHS number, date of birth and postcode is collected by the sites and stored on an encrypted table within the main study database. Section 7 details the consent procedure in place for collection of PID.

Raw data extracts received from the digital registries will either be sent linked to the IBIS-II study number and PID removed by the data registry beforehand or it will be sent containing PID. This will depend on the specific policy of the data organisation.

When PID is sent to the IBIS-II research team from a data registry, a suitably qualified person will pseudonymise the datasets by linking the data to the existing IBIS-II dataset and remove all PID prior to further processing by the IBIS-II data management team to minimise unmerited access to PID. All raw datasets are considered source data and should be stored for the duration of the study and archiving period. This data will be stored on an encrypted, un-networked computer at the Wolfson Institute of Preventive Medicine. The ICD-10 code list of events (Table 1) will be used to match events with further details on deaths, new or recurrent breast cancers from variables listed in Table 2.

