### **SAEs during the follow up period:**

SAEs which are an event of interest (see section 4.5.1.2), should continue to be collected and reported to the IBIS-II CCO after a patient has completed active treatment i.e. during the annual post-treatment follow-up period by the PI/delegated clinician under expedited timeframes. AEs/SAEs in clinical areas other than those pre-specified will not be actively sought or collected within CRFs during the follow up period and should not be sent to IBIS-II CCO. However, if an investigator becomes aware of a SAR during the follow up period i.e. meets the definition of an SAE and in the investigator's judgement has a causal relationship to a study IMP, this should be reported by the investigator to the IBIS-II team using expedited reporting timeframes, regardless of whether the SAE is a clinical event of interest.

What to report as an SAE in the long term follow up period under expedited conditions:

- ✓ Cerebrovascular event/Stroke/TIA
- ✓ New primary cancers (except basal cell carcinoma, squamous cell carcinoma of the skin and carcinoma in situ of the cervix)
- ✓ Cardiovascular events e.g. angina, myocardial infarction
- ✓ Thromboembolic events e.g. deep vein thrombosis, pulmonary embolism, phlebitis
- ✓ Osteoporosis/Broken/fractured bone
- ✓ Deaths (including underlying cause of death)
- ✓ Any other AE meeting the definition of serious (see above) and in the opinion of the investigator is causally related to the IMP i.e. **all SARs**

What not to report as an SAE in the long term follow up period:

- ✗ New breast cancer or DCIS (endpoint not SAE)
- ✗ AEs that do not meet the definition of serious
- ✗ Pre-planned hospitalisations/elective surgery where the underlying condition does not meet the definition of an SAE
- ✗ Non-protocol specified SAEs (see above) that are not in the opinion of the investigator, related to the IMP

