### **Closed UK sites**

There are limitations of registry data collection, in that seriousness and relatedness cannot be assessed by this method of data collection once the sites have closed. A risk adapted approach is now merited as the safety profile of anastrozole is well-established across multiple trials and long follow up periods (as of 31 July 2016, the total cumulative exposure

figure for Arimidex (anastrozole) in the marketed setting is calculated to be in excess of 8 million patient years). Anastrozole has also been recommended by the National Institute of Clinical Excellence (CG164) as a first-line therapy for women at risk of breast cancer without osteoporosis. All participants are now off-treatment and the half-lives of anastrozole is relatively short (50 hours), therefore collection of follow up data from the digital registries poses a minimal risk to participants.

All data received via registries in the UK will be assessed by the data management (DM) team as part of a bulk dataset. This long-term follow-up data will be received by an independent data manager on a yearly basis from the various devolved UK data registries and Public Health England as previously described. The data will be screened for deaths, new and recurrent breast cancers and other ICD-coded events listed in Table 1. All newly identified events that meet the criteria listed in 4.5.1.2 will be sent to AZ as an 'unverified' line listing once a year. This will provide data on AEs that should be reported in the long term follow up period under expedited conditions but with the limitations discussed above.

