Antipyrine, warfarin and cimetidine clinical interaction studies indicate that the co-administration of anastrozole with other drugs is unlikely to result in clinically significant drug interactions mediated by cytochrome P450.

Hepatic changes (elevated gamma-GT or less commonly alkaline phosphatase) have been reported in patients with advanced breast cancer, many of whom had liver and/or bone metastases. A causal relationship for these changes has not been established. Slight increases in total cholesterol have also been observed in clinical trials with anastrozole.

Daily doses of anastrozole up to 10 mg do not have any effect on cortisol or aldosterone secretion, measured before or after standard ACTH challenge testing. Corticoid supplements are therefore not needed.

Events of Carpal Tunnel Syndrome have been reported in patients receiving anastrozole treatment in clinical trials in greater numbers than those receiving treatment with tamoxifen. However, the majority of these events occurred in patients with identifiable risk factors for the development of the condition.

In the ATAC trial, ischaemic cardiovascular events were reported more frequently in patients treated with anastrozole compared to those treated with tamoxifen, although the difference was not statistically significant. The observed difference was mainly due to more reports of angina pectoris and was associated with a sub-group of patients with pre-existing ischaemic heart disease.

Sensory disturbances (including paraesthesia, taste loss and taste perversion) have been reported more frequently in patients receiving anastrozole than those on tamoxifen in clinical trials. In order to ensure that participants still on treatment are aware of this

newly listed side effect (added to Arimidex Summary of Product Characteristics [SmPC] v160114), they must be informed of this at their next clinic appointment.

The full list of adverse reactions to anastrozole is available as a separate document. (Astra Zeneca Core Data sheet)

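### Table 1 codes hypertension with the ICD-10 code for angina and leaves out essential hypertension, so it cannot capture both events that section 4.5.1.2 names

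*Protocol*

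**What the plan says.** Protocol section 4.5.1.4 uses Table 1 to turn registry records into trial events. It states that "The ICD-10 code list of events (Table 1) will be used to match events". In that table the Hypertension row reads "I20, I15 (all sub-codes), I27 (all sub-codes"), and the acute myocardial infarction row reads "I21 (all sub-codes), I22 (all sub-codes"). No row is named angina, and I10, I11, I12 and I13 are not listed anywhere.

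The follow-up events are described elsewhere in clinical terms. Section 4.5.1.2 asks women about "Cardiovascular events e.g. angina, heart attack, hypertension". The list of what to report as an SAE in follow-up (section 4.5.4.2) has "Cardiovascular events e.g. angina, myocardial infarction".

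For closed UK sites, section 4.5.4.3 says: "The data will be screened for deaths, new and recurrent breast cancers and other ICD-coded events listed in Table 1". Section 4.5.1.4, on the scope of UK registry data, adds that once a UK site closes, long-term data come from the digital registries alone. The aim that these codes serve is in section 1.2: "To examine the effect of anastrozole on other cancers, cardiovascular disease, fracture rates, and non-breast cancer deaths".

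**The concern.** The code list and the list of events of interest do not describe the same events. A filter built on Table 1 as printed would put angina under the wrong name and would not pick up the common form of hypertension.

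Two outputs depend on it. One is the cardiovascular part of the secondary aim, for UK women whose sites have closed. The other is the yearly unverified line listing sent to the manufacturer, in which a reader would take angina for hypertension or would not see it at all. Angina is not a marginal item in this protocol. Section 5 says of the ischaemic events in the large adjuvant trial: "The observed difference was mainly due to more reports of angina pectoris".

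**Working it through.** No sample size, power or event figure is involved, so the check sets the code list beside the event list.

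**Inputs.** The codes are from Table 1. The coding system, ICD-10, is named in section 4.5.1.4. The events are from sections 4.5.1.2 and 4.5.4.2. The category titles are those of ICD-10 itself and are not printed in the protocol: I10 essential hypertension, I11 to I13 its heart and kidney forms, I15 secondary hypertension, I20 angina pectoris, I27 other pulmonary heart diseases (which include pulmonary hypertension).

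**Step 1: the row as printed.** Of the three categories listed under Hypertension, only I15 is systemic hypertension. I20 belongs with ischaemic heart disease and comes directly before the I21 and I22 infarction codes that Table 1 itself uses. I27 is pulmonary.

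**Step 2: could I20 be a slip for I10?** Probably. It is the only code in its row without the note that all sub-codes are included. That fits I10, which has none, and does not fit I20, which has several. The document cannot confirm it, so both readings are carried forward.

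**Step 3: what the filter would do with a registry record.**

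| Record | I20 as printed | I20 a slip for I10 |
|---|---|---|
| Angina (I20) | extracted, labelled Hypertension | matches no row |
| Essential hypertension (I10) | matches no row | extracted, labelled Hypertension |
| Hypertensive heart or kidney disease (I11 to I13) | matches no row | matches no row |
| Secondary hypertension (I15) | labelled Hypertension | labelled Hypertension |
| Pulmonary heart disease (I27) | labelled Hypertension | labelled Hypertension |
| Infarction (I21, I22) | correct | correct |

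In neither column are angina and essential hypertension both captured under their own names. Pooling all cardiovascular rows does not cure this: the total lacks I10 in the first column and I20 in the second.

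**Step 4: is there another route?** For UK women after closure the registries are the only source. The GP follow-up in section 4.5.1.4 is for further detail on breast cancers. Open international sites still ask about angina and hypertension by name. The raw extracts are kept for the study and the archiving period, so a wrong filter can be put right.

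**The case against.** The strongest reply is that this is one mistyped digit. If I10 was meant and the working filter uses it, essential hypertension is captured, no angina is mislabelled, and what remains is a missing angina row. Import runs under a data management plan that is not shown, so nothing proves that a wrong filter was run or a wrong listing sent. This stands, and it is why the consequences are put conditionally. It does not clear the table, because the slip reading leaves angina without a code.

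Second, a wrong label is not lost data: as printed, I20 is still extracted and can be relabelled. That also stands, but it does not help with I10.

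Third, UK registry capture rests on in-patient and A&E data. Hypertension managed outside hospital would be missed even with I10 listed, so the correction will not make registry and questionnaire data equivalent. This is right and limits what the fix can achieve.

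Fourth, I27 includes pulmonary hypertension, so placing it under Hypertension is arguable. It is enough to show it separately.

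A reader might go further and use Table 5, where ischaemic cardiovascular disease is 2.5% on anastrozole and 1.9% on tamoxifen, as the size of what this row distorts. The documents do not support that. Those figures cover all ischaemic disease, not angina alone, and come from a comparison with tamoxifen in adjuvant patients. Section 5 adds that the difference was not statistically significant and was associated with patients who already had ischaemic heart disease. Nor does the protocol define an ischaemic composite, or a separate angina or hypertension comparison, that this row could be said to invalidate.

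**Conclusion.** The point holds as a coding error in a table that the trial relies on. On either reading of I20, Table 1 cannot deliver both angina and hypertension as section 4.5.1.2 names them. Angina, which section 4.5.4.2 lists as reportable, is either mislabelled or absent.

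The reach is limited to registry capture, and chiefly to UK women after site closure. What is affected is any component breakdown under the secondary cardiovascular aim and the safety line listings. The primary endpoint and the power are unaffected. Because one code list serves both arms, the error by itself does not favour either. It would be tempting to infer that mislabelled listings have already gone out, but the protocol does not show this.

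No number of events can be given, since the protocol reports no registry counts for angina or hypertension. The conclusion rests on the standard ICD-10 titles. The absence of any row named angina can be seen without them. It should be fixed before the final analysis, but it does not threaten the trial's main result.

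**What to change.** Reconcile Table 1 with section 4.5.1.2:

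- Hypertension: I10, I11 to I13, and I15 (all sub-codes).
- A new Angina row: I20 (all sub-codes).
- I27 shown separately from systemic hypertension.

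Then establish which codes the working filter actually used, re-run it on the retained raw extracts, and correct past line listings if any were affected. State in the report that registry hypertension means hypertension coded in hospital data.

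The cost is a table edit and a small re-run. If the data requests were limited to the listed codes, the missing ones would have to be added at the next annual extract. Hypertension managed outside hospital will still be missed.

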#### Data collection and storage

Data will be collected annually via the UK-based digital registries and as negotiated with the international sites (where applicable). No data will be exported outside the EU or the UK. Data collected from international sites will be stored according to the terms outlined in the DSA.

Long-term follow-up data received from national registries will be processed and held on a secure Barts Cancer Centre IT network. Data registry variables specified in Table 1 will be used to capture breast cancers, deaths, other cancers, cardiovascular, cerebrovascular, and fractures to meet the study objectives. Supplemental information on tumour markers will be collated from national and devolved cancer registry datasets (Table 2).

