### **Scope of UK registry data collection**

Digital registry flagging is used for the UK cohort for the full duration of follow up provided valid consent (or CAG exception) is in place as described in section 4.5.5.3. While a UK site is open, registry data will be collected to confirm and underpin site-reported events. Once the site is closed, long term data collection will transition to data collection via the UK digital registries only.

HES covers all NHS Clinical commissioning groups (CCGs) in England and Wales including private patients treated in NHS hospitals, patients' resident outside of England under care provided by treatment centres, including the independent sector, funded by the NHS. For participants who commenced the study in England and moved to either Northern Ireland or Scotland, cross-border transfers will be recorded so they can be followed up via the appropriate national registry (NSS or NICR). Similarly, if participant moved from the devolved nation to England this will also be detected.

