### **6.2 Endpoints**

The primary endpoint is the development of locally histologically confirmed breast cancer, both invasive and non-invasive (i.e. including DCIS). The principal analysis for comparing the active treatment to placebo will be performed when 117 cases of breast cancer have been diagnosed in the prevention stratum (see section 6.3 for more details). It is anticipated that this will occur after a median follow-up of 5 years. Primary endpoint data will be collected from participating women until the end of trial definition (LPLT + 5 years of follow up).

Adherence to treatment protocol will cease if a woman develops breast cancer and a breast cancer CRF should be returned. All breast cancer pathology must be reviewed by a pathologist approved by the UK National Breast Screening Programme or foreign equivalent. In addition, a tissue block or where unavailable 20 sections. will be required in consenting women for all breast tumours developing after entry into the trial.

It is recognised that breast cancer mortality is an important exploratory endpoint and this will also be analysed. However, the power to detect this within 10 years is marginal. Continued long-term follow-up beyond 10 years, as well as an overview of other similar trials will be needed to obtain clear results on this question. Total and cause-specific mortality will be analysed and the Final CRF (if still on active treatment) and Death CRF should be returned for any woman who dies of any cause while on therapy.

All women will be followed up for cancer incidence (breast and other cancers) and cause of death using available NHS registries as described in section 4.5.1.4. During the 5-year period of active follow-up and the post-treatment follow-up period serious medical conditions will be recorded including myocardial infarction and other heart problems, thromboembolic events (superficial and deep), cardiovascular events, osteoporosis, fractures, and other cancers.

Basic information on prescriptions and hospital visits during the 5 years of active treatment for each participant will also be recorded.

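### Osteoporosis is a listed post-treatment event, but the registry code list used after UK site closure has no row for osteoporosis without fracture

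*Protocol*

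**What the plan says.** Three sections make osteoporosis something to collect after treatment.

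- Protocol 4.5.1.2 has a combined bullet for osteoporosis and fracture in its list of post-treatment events. It justifies the short list by saying which effects may outlast the drug: "Except for certain conditions (endometrial cancer, osteoporosis/fracture, cardiovascular disease".
- Protocol 4.5.4.2, on SAEs during follow-up, repeats the combined bullet: "Osteoporosis/Broken/fractured bone".
- Protocol 6.2 lists the two as separate items among the serious medical conditions recorded in both the active and post-treatment periods: "thromboembolic events (superficial and deep), cardiovascular events, osteoporosis, fractures, and other cancers".

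For UK women the source then changes. Under Scope of UK registry data collection (4.5.1.4), once a site is closed "long term data collection will transition to data collection via the UK digital registries only". The same section says that Table 1 is the list used to match events. Section 4.5.4.3 (Closed UK sites) screens the extracts for deaths, breast cancers and Table 1 codes, and sends AstraZeneca a yearly listing of new events meeting the 4.5.1.2 criteria.

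Table 1 has no osteoporosis row. Its only M code opens the Fractures row: "M80 (all sub-codes), T02.9, T08, T10, T12". Data collection and storage describes the purpose of the registry variables as being to "capture breast cancers, deaths, other cancers, cardiovascular, cerebrovascular, and fractures to meet the study objectives".

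**The concern.** The event list and the code list do not agree, and after UK closure only the code list operates. Whatever Table 1 does not code is not found, even if 4.5.1.2 lists it.

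The item lost belongs to a safety domain that the protocol takes seriously. Section 5 says that managing potential bone loss is likely to be important, 4.1.2 requires a baseline DXA scan for every woman, and 4.5.1.2 puts osteoporosis and fracture among the few effects not expected to end at washout. Open international sites continue with the questionnaire and still ask about osteoporosis. Ascertainment therefore depends on country and on site closure date. A fall in recorded osteoporosis after closure could reflect the code list and not the women's health, and a reader of the yearly listing would see no cases without being told that none were looked for.

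**Working it through.** No figure in the plan bears on this and no calculation applies. The check sets the event list, the code list and the rules for closed UK sites side by side.

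1. **Is osteoporosis to be collected after treatment?** Yes, in three sections: 4.5.1.2, 4.5.4.2 and 6.2. Only 6.2 separates it from fracture. Sections 4.5.4.2 and 6.2 are limited to serious events or conditions. The 4.5.1.2 list is not: it is what participants are asked about.

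2. **Does Table 1 code it?** Rows for osteoporosis: 0. M codes in the table: 1 (M80), in the Fractures row. The protocol does not define M80. In ICD-10 it is osteoporosis with pathological fracture, which fits its place in that row. The missing row is visible without that definition.

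3. **Is there another route after UK closure?**
   - Site questionnaire: ended, since collection moves to registries only.
   - GP contact (4.5.1.4, Following up with GPs): described for new or recurrent breast cancers.
   - Retained raw extracts (4.5.1.4): kept as source data, but no search beyond Table 1 is planned.

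4. **Does the protocol declare the narrowing?** Section 4.5.4.3 names the limitations of registry data as the inability to assess seriousness and relatedness. It does not say that a listed event type drops out, and it still refers to the 4.5.1.2 criteria. Table 1 is headed as events of interest, the term that 4.5.4.2 uses for the 4.5.1.2 list, and it carries other items from that list, such as TIA and hypertension.

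5. **What follows?**

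| Follow-up | Osteoporosis with fracture | Osteoporosis without fracture |
|---|---|---|
| Open international sites (questionnaire) | collected | collected |
| Closed UK sites (registry, Table 1) | found through the Fractures row, if hospital-coded | not identified |

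The listing in 4.5.4.3 is drawn from events already found by the Table 1 screen, so it cannot contain the lower right-hand cell.

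**The case against.** The strongest reply is that the registry scope was meant to be narrower. Data collection and storage names fractures and not osteoporosis, Table 3 lists bone fractures among what HES provides, and the secondary aim in 1.2 is fracture rates. Osteoporosis appears in no aim, and bone density is assigned to separate protocols. Sections 4.5.1.2 and 4.5.1.3 also state openly that closed sites follow a different procedure. The reference in 4.5.4.3 to the 4.5.1.2 criteria can be read as a filter on events already found, not as a promise to find every listed item.

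Much of this stands. The stated bone objective is covered by Table 1, and nothing in the aims is lost. But the narrowing is nowhere stated for osteoporosis, and 4.5.1.2, 4.5.4.2, 4.5.4.3 and 6.2 still read as if it were collected. Even if intended, it needs to be written down.

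It is also fair that adding a code would recover only part of the loss. HES supplies admitted-patient and A&E data, so osteoporosis diagnosed only in outpatient or primary care would still be missed.

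A reader might go further than the documents allow in three ways:

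- **That all three sections list osteoporosis separately from fracture, or ask for every case.** Only 6.2 separates it, and 4.5.4.2 and 6.2 are limited to what is serious. Serious osteoporosis without fracture is nevertheless missed too.
- **That bone loss is the main expected harm.** Section 5 does not say so. It calls the extent of bone loss unclear and also names musculoskeletal symptoms, for which Table 5 shows 27.8% on anastrozole against 21.2% on tamoxifen.
- **That such events can never be recorded for UK women.** Site data from before closure remain, and the raw extracts are kept. The gap is in the planned screen.

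**Conclusion.** The inconsistency is real and should be corrected. Its reach is limited: after UK site closure the plan does not identify osteoporosis without fracture, while open international sites do. Post-treatment osteoporosis counts will be incomplete, and registry-only and site-based follow-up cannot be compared on this event. The primary endpoint and the fracture-rate aim are unaffected.

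No size can be given. One might infer that the pooled rate, and the absolute excess on anastrozole, are understated by the UK registry-only share of post-treatment person-time. With share *u* and a common true rate *r*, the observed pooled rate would be (1 − *u*) × *r*. The protocol gives no value for *u* and specifies no pooled post-treatment osteoporosis analysis, and the step assumes equal rates, and an equal excess, in UK and other women. Nor do the documents support a claim of bias towards one arm: the same code list applies to both, and randomisation is stratified by hub centre, so the gap does not by itself favour either.

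The conclusion rests on reading Table 1 as the operative screen, as 4.5.1.4 and 4.5.4.3 say, and on the standard ICD-10 meaning of M80.

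**What to change.** Reconcile the event list and the code list in one of two ways.

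1. **Collect it.** Add a Table 1 row for osteoporosis without fracture (ICD-10 M81) and re-run the match on the retained extracts, as far as they carry the code. Report registry and questionnaire rates separately, and label the registry rate a lower bound because HES covers only in-patient and A&E care. The cost is one row and one repeat of the match. The remaining weakness is under-recording in hospital data.

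2. **Declare that it is not collected.** State in 4.5.1.2, 4.5.4.2, 4.5.4.3 and 6.2 that osteoporosis without fracture is not collected after UK site closure, and censor any analysis of it at the end of site-based follow-up. The cost is a few sentences and the loss of UK follow-up time for this event.

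Either is adequate. The second gives one consistent method of ascertainment. The first keeps some information on UK women and lets the yearly listing include the event. Under either, the yearly listing to AstraZeneca should say which 4.5.1.2 items the registry screen can and cannot find.
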